#### Correlation analysis

2.8.4.

Spearman correlation analysis will be employed to explore the correlations between gray matter volume, gut microbiota, TMAO levels, and primary and secondary outcomes, respectively, in order to preliminarily reveal the potential mechanisms underlying the infrared moxibustion intervention effects. Bonferroni correction will be applied to adjust for multiple comparisons.

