**Patient and methods:**

This study will recruit 158 patients with mild hyperlipidemia and randomly assign them to either a genuine infrared moxibustion group or a sham infrared moxibustion group. The intervention will be administered twice weekly for a total of 8 weeks. Blood lipid levels, Montreal Cognitive Assessment scores, Hamilton Depression Rating Scale scores, Hamilton Anxiety Scale scores, and Pittsburgh Sleep Quality Index scores will be compared between the two groups before treatment, and at 4, 8, and 12 weeks post-treatment. Additionally, changes in gut microbiota, the gut microbiota metabolite trimethylamine N-oxide (TMAO), and brain gray matter volume will be detected and compared between the two groups before treatment and at 8 weeks post-treatment (See Graphic Abstract).

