An increasing number of scholars have proposed correlations between gut microbiota and their metabolites with HLP. Dysbiosis of the gut microbiota may serve as a mediating factor in the causal relationship between a high-calorie diet and CD [22]. Xia M et al. revealed that, compared to healthy volunteers, the mixed fecal samples from elderly HLP patients were predominantly composed of *Firmicutes* and *Proteobacteria*, with an increased relative abundance of *Helicobacter, Lactobacillus*, and *Desulfovibrio*, and a decreased relative abundance of *Parabacteroides, Bacteroides, Blautia, Bifidobacterium*, and *Peptococcus* [23]. Among the metabolites produced by the gut microbiota, trimethylamine-N-oxide (TMAO) has garnered considerable attention for its involvement in the regulation of lipid metabolism and inflammatory responses, and is recognized as a risk factor for HLP [24]. Numerous animal experiments and clinical studies have demonstrated that a high-fat diet increases TMAO production [25–27]. Fei’erdun T et al. discovered that HLP patients exhibited higher plasma levels of TMAO compared to those with normal lipid profiles, with its concentration showing a positive correlation with TG and a negative correlation with high-density lipoprotein cholesterol HDL-C [27]. A high-fat diet may trigger or exacerbate the onset of cognitive impairment by increasing the abundance of harmful bacterial genera and TMAO levels, while simultaneously reducing the abundance of beneficial bacterial genera [28]. Our previous research indicated that TMAO is involved in the pathogenesis of mild cognitive impairment (MCI) and can serve as a biomarker and therapeutic target for MCI [29]. Furthermore, TMAO and its precursor substances have been confirmed by multiple studies to be associated with brain volume changes, cognitive decline, and an increased risk of dementia [30–32]. Yaqub A and colleagues proposed that elevated levels of TMAO-related metabolites may induce brain atrophy, thereby increasing the risk of dementia [30]. Existing evidence shows that traditional moxibustion can reduce the levels of TMAO in animals fed a high-fat diet and improve their lipid profiles. Moreover, changes in its precursor substances exhibit a significant correlation with specific bacterial groups [33,34]. Moreover, a study has observed that acupuncture intervention can induce alterations in brain structure in obese patients and animals on a high-fat diet [35], suggesting that acupuncture and moxibustion therapies may participate in metabolic regulation by influencing the central nervous system.

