#### Primary outcomes

2.5.1.

The change in LDL-C from baseline to 8 weeks after intervention.

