##### Plasma TMAO

2.5.3.2.

Participants will fast starting at 8 PM the night before blood collection. At 8 AM the next morning, a 6 mL fasting venous blood sample will be drawn from the elbow vein after 12 h of fasting. Of this, 3 mL will be centrifuged to obtain serum for lipid measurement; the other 3 mL will be anticoagulated and centrifuged to obtain plasma samples, which will be immediately placed in a −80 °C freezer for TMAO detection. Changes in TMAO levels in participants will be detected at baseline and after 8 weeks of treatment. Plasma TMAO content will be detected using liquid chromatography-mass spectrometry, with TMAO content quantified by peak area. Larger peak areas indicate higher TMAO content.

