#### MRI analysis

2.8.3.

To explore whether baseline brain structure is correlated with clinical phenotypes, voxel-based morphometry (VBM) will be employed to analyze the correlation between baseline gray matter volume and primary and secondary observed outcomes across all participants on a whole-brain scale. Age, sex, years of education, and total intracranial volume will be included as covariates in the regression model for control. Multiple comparison correction will be performed at the whole-brain voxel level using family-wise error rate (FWE), with a voxel-level P_FWE_ < 0.05 considered statistically significant.Based on the brain regions showing significant correlations in analysis (1), gray matter volume in these regions was extracted for each participant to construct regions of interest (ROIs). A two-sample *t*-test was used to compare differences in gray matter volume between the two groups within the aforementioned ROIs, with age, gender, years of education, and total intracranial volume included as covariates. The Bonferroni method was used for multiple comparison correction.

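### The mechanism analysis in section 2.8.4 uses pooled Spearman correlations that ignore arm and are not put on the change scale, so it shows association rather than how the intervention works

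*Protocol article*

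**What the plan says.** Section 2.8.4 (Correlation analysis) gives the method: "Spearman correlation analysis will be employed to explore the correlations between gray matter volume, gut microbiota, TMAO levels, and primary and secondary outcomes". It gives the purpose in the same sentence: "in order to preliminarily reveal the potential mechanisms underlying the infrared moxibustion intervention effects". On multiplicity it says: "Bonferroni correction will be applied to adjust for multiple comparisons". It names no visit, no arm term and no stratification by arm, and it does not say whether the markers enter as levels or as changes.

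Other sections bear on how to read this:

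- Section 2.5.1 defines the primary outcome as a change: "The change in LDL-C from baseline to 8 weeks after intervention". Section 2.5.2 gives no such definition for triglycerides, total cholesterol, HDL-C, MoCA, HAMD, HAMA or PSQI.
- Section 2.5.3.2 has TMAO measured twice: "Changes in TMAO levels in participants will be detected at baseline and after 8 weeks of treatment". Stool samples and MRI are also taken at baseline and week 8 (sections 2.5.3.1 and 2.5.3.3, Table 1).
- The abstract plans a comparison of the markers between arms, including "brain gray matter volume will be detected and compared between the two groups before treatment and at 8 weeks post-treatment". Section 2.8.3 plans to "compare differences in gray matter volume between the two groups within the aforementioned ROIs".
- The Introduction reports a cross-sectional finding for TMAO in hyperlipidemia, "with its concentration showing a positive correlation with TG and a negative correlation with high-density lipoprotein cholesterol HDL-C".
- Section 2.4.2 gives both arms the same lifestyle programme, including diet.

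**The concern.** The trial's mechanistic hypothesis is about what treatment changes: microbiota, TMAO and brain volume move, and lipids move with them. A correlation computed over all participants without regard to arm does not address that.

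Two distinct faults can arise. First, if levels are correlated with levels, the result reflects stable differences between people. The Introduction says such differences exist for TMAO with TG and HDL-C, so a significant result could be expected whether or not the device works. Second, if changes are correlated but the arms are pooled, two variables that both respond to treatment will correlate even when they are unrelated within either arm.

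In either case a significant coefficient could be reported as support for the gut-brain mechanism although it carries no such information.

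**Working it through.** Section 2.8.4 states no figure to reproduce, and the documents give no correlation coefficients. The sizes below rest on assumptions and show how the method behaves; they do not predict this trial.

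**Set-up.** N = 158 in a 1:1 ratio (sections 2.7 and 2.2), two visits. Assumed: each variable is a stable personal part (SD 1) plus an independent visit part (SD 0.6). 3,000 simulated trials per setting, two-sided p<0.05.

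**1. Level against level at week 8, no intervention effect.** The correlation between observed levels is the stable correlation × 1/(1 + 0.6²) = stable correlation / 1.36. Analytic check: SE = √(1.06/155) = 0.0827, and the chance of significance is about Φ(atanh(r)/SE − 1.96).

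| Stable correlation | Observed r | atanh(r)/SE | Analytic | Simulated |
|---|---|---|---|---|
| 0.2 | 0.147 | 1.79 | 43% | 43% |
| 0.3 | 0.221 | 2.71 | 77% | 76% |
| 0.4 | 0.294 | 3.66 | 96% | 94% |

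At N = 132 the simulated range is 37% to 90%. Adjusting for arm leaves the N = 158 rates at about 43%, 76% and 94%, because under a null intervention arm explains nothing.

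**2. Same null trials, other scales.** Change against change: about 5%. Marker level (baseline or week 8) against outcome change: about 5% to 6%. The second result covers LDL-C as section 2.5.1 defines it.

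**3. Bonferroni.** The number of tests is not stated. Counting each marker once gives 3 markers × 8 outcomes = 24 tests, critical z = 3.08. The three rates in step 1 become Φ(1.79 − 3.08) = 10%, Φ(2.71 − 3.08) = 36% and Φ(3.66 − 3.08) = 72%. Several microbiota measures would raise the count and lower these rates. With 50 tests (z = 3.29) they are 7%, 28% and 65%. The correction reduces the problem but does not remove it.

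**4. Treatment shifts both variables, with no link within arm.** With a shift of 0.8 in each, the within-arm SD of change is 0.6 × √2 = 0.849, so the shift is δ = 0.943 SD. The pooled correlation of changes is (δ²/4)/(1 + δ²/4) = 0.222/1.222 = 0.18. It is significant in about 60% of trials analytically and 64% in simulation. With a shift of 0.5 the simulated rate is 15%. Adjusting for arm returns both to about 5%.

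**5. Shared change in both arms, no intervention effect.** If the visit parts of marker and outcome correlate at 0.3, for example through lifestyle change, change against change is significant in 95% of trials, and still in 95% after adjusting for arm. A test of arm on the marker is significant in only about 5%. Change scores with arm adjustment are therefore not enough for a mechanism claim; an arm effect on the marker is also needed.

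**The case against.** The strongest reply is that the article does not commit to levels. A reader might infer that the plan makes no use of change, but the primary outcome is a change score, section 2.5.3.2 speaks of changes in TMAO, and section 2.8.4 is silent on scale for the markers. For LDL-C the level-by-level rates do not apply; a marker level against LDL-C change stays near 5% to 6% under the null if visit-to-visit parts are independent. This stands, and it confines the first fault to the seven outcomes not defined as change.

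A reader might also infer that section 2.8.4 is the only analysis tying markers to outcomes. It is not: section 2.8.3 relates baseline gray matter volume to the outcomes, and the abstract and section 2.8.3 plan comparisons between arms. Those comparisons show whether a marker moved. They do not show whether its movement goes with the lipid response.

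The document also hedges. Section 2.5.3 calls the markers exploratory, section 2.8.4 calls the reading preliminary, and the limitations in the Discussion restrict the microbiota-lipid correlation to association. These hedges lower the certainty claimed but do not alter what is estimated, and the Discussion caveat does not extend to TMAO or gray matter.

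Finally, visit and scale may be left to a fuller plan. Silence on those details alone would not be a finding. But the article does fix both a method (bivariate Spearman, no arm) and a purpose, and the two do not fit. Section 2.8.3 shows that it names visit and covariates where they are planned.

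**Conclusion.** The point holds in limited form. Section 2.8.4 as written can show association, not the mechanism of an intervention effect. For the three other lipids and four scales, level-by-level correlation would be significant in about 43% to 94% of null trials at N = 158 before multiplicity correction. For changes, pooling the arms can create a correlation when treatment moves both variables.

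The documents do not support saying that the missing arm adjustment produces a false mechanism when the device does nothing: in that case adjustment makes no difference, and the scale is what matters. Arm matters when treatment shifts both variables.

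All correlations, variance components and effect sizes are assumptions. The Introduction reports TMAO's association with TG and HDL-C without coefficients and gives none for LDL-C. The primary efficacy analysis is untouched, but the mechanistic conclusions depend on this section, so it should be changed.

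**What to change.** In section 2.8.4:

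1. Correlate the baseline-to-week-8 change in TMAO, named microbiota measures and gray matter volume with the change in LDL-C and each secondary outcome over the same interval.
2. Use partial Spearman correlation adjusted for arm, and also show the correlation within each arm.
3. Report level-by-level correlations as descriptive association only.
4. Read a marker as a possible mechanism only if the planned comparison between arms also shows an arm effect on that marker, because shared lifestyle change can make changes correlate with no device effect.
5. If this is not adopted, replace the mechanism wording with association for all markers, as the Discussion already does for microbiota and lipids.

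The cost is a few sentences; markers and outcomes are already scheduled at both visits. The drawback is that change scores carry more measurement error, so real associations may look weaker.

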#### Inclusion criteria

2.3.2.

(1) Meet the diagnostic criteria for hyperlipidemia; (2) Aged between 18 and 70 years; (3) Not currently using lipid-lowering medications, or have discontinued lipid-lowering medications for at least one month, and are not participating in other clinical studies; (4) Sign an informed consent form.

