### Sample calculation

2.7.

The sample size for this study was calculated using G*Power 3.1.9.7 software based on existing research on moxibustion for treating hyperlipidemia. According to previous trial results [37], the LDL-C levels after intervention in the moxibustion group and the control group were 4.41 ± 0.52 mmol/L and 3.72 ± 0.43 mmol/L, respectively. With a two-tailed test value of α = 0.05 and a power of 0.95, the sample size per group was calculated to be *n* = 66. Considering a 20% dropout rate, the required sample size per group is 79, resulting in a total required sample size of 158 for this study.

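### Section 2.8.4 correlates gray matter volume with the outcomes without the covariates that 2.8.3 uses for gray matter volume, so level-on-level correlations can reflect shared dependence on age

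*Protocol article*

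**What the plan says.** Two adjacent sections of the protocol article deal with gray matter volume and the clinical outcomes.

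- **Section 2.8.3, MRI analysis.** The first step is to "analyze the correlation between baseline gray matter volume and primary and secondary observed outcomes across all participants on a whole-brain scale". For this model, "Age, sex, years of education, and total intracranial volume will be included as covariates in the regression model for control". The later comparison of the two groups within regions of interest is again made "with age, gender, years of education, and total intracranial volume included as covariates".
- **Section 2.8.4, Correlation analysis.** Here "Spearman correlation analysis will be employed to explore the correlations between gray matter volume, gut microbiota, TMAO levels, and primary and secondary outcomes". The only safeguard named is that "Bonferroni correction will be applied to adjust for multiple comparisons". The stated purpose is "in order to preliminarily reveal the potential mechanisms underlying the infrared moxibustion intervention effects". The section gives no covariates, no time point, no regions and no number of tests, and it does not say whether levels or changes are correlated.

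Eligibility (2.3.2) is wide in age: "Aged between 18 and 70 years". The primary outcome (2.5.1) is defined as a change in LDL-C over 8 weeks. The secondary outcomes (2.5.2) are listed without being defined as changes.

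**The concern.** The plan treats age, sex, education and head size as needing control whenever gray matter volume is analysed in 2.8.3. It then names a method for gray matter volume in 2.8.4 that controls none of them. If volume and an outcome both vary with age, their simple rank correlation is non-zero even when nothing else links them. Bonferroni lowers the chance that random noise crosses the threshold. It does nothing to a correlation that is really present in the data because of a common cause.

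What is at stake is the mechanistic reading of the trial, since 2.8.4 is the analysis meant to point to mechanisms. A correlation between volume and MoCA, or between volume and a lipid, could be reported as a lead when it reflects only the age mix of the sample. For correlations of baseline levels, 2.8.3 and 2.8.4 could also give different answers about the same variables, and the article does not say which would take precedence.

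**Working it through.** The article states no figure on this point, so there is nothing to reproduce. The check asks how often a plain Spearman test would be significant if age were the only link between volume and outcome.

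**Inputs from the article**
- Sample size (2.7): "the required sample size per group is 79, resulting in a total required sample size of 158 for this study". The stated dropout is 20%, so 158 × 0.8 = 126.4, about 126 with follow-up data. Both 126 and 158 are used.
- Two-sided level 0.05. This is stated in 2.8.2 and assumed to apply in 2.8.4.
- Bonferroni (2.8.4). The number of tests is not given. I use m = 8, one test for each of LDL-C, TG, TC, HDL-C, MoCA, HAMD, HAMA and PSQI, so the threshold is 0.05/8 = 0.00625.

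**Assumptions (the article gives no values)**
- Levels are correlated with levels.
- The absolute correlation with age is *a* for gray matter volume and *b* for the outcome. Three pairs are shown to give a range: (0.5, 0.2), (0.6, 0.25) and (0.6, 0.4).
- There is no direct link between volume and outcome.

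**Formulas**
1. Induced Pearson correlation: r = a × b.
2. Spearman equivalent: ρ = (6/π) × arcsin(r/2).
3. Standardised size: λ = atanh(ρ) / √(1.06/(n − 3)).
4. P(significant) = Φ(λ − c) + Φ(−λ − c), with c = 1.96 for one test and c = 2.734 at 0.05/8.

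**Worked case: a = 0.6, b = 0.25, n = 126**
- r = 0.6 × 0.25 = 0.15; ρ = 0.143; atanh(ρ) = 0.144.
- √(1.06/123) = 0.0928, so λ = 0.144/0.0928 = 1.555.
- At 0.05/8: Φ(1.555 − 2.734) = Φ(−1.179) = 0.119. The second term is negligible.

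**Results.** The approximation is shown for n = 126 and n = 158. The last column gives simulations with age uniform on 18 to 70.

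| a, b | r | One test at 0.05 | At 0.05/8 | Simulation at 0.05/8 |
|---|---|---|---|---|
| 0.5, 0 | 0 | 5%, 5% | 0.6%, 0.6% | about 0.6% |
| 0.5, 0.2 | 0.10 | 18%, 21% | 4%, 6% | 5-7% |
| 0.6, 0.25 | 0.15 | 34%, 42% | 12%, 16% | 13-18% |
| 0.6, 0.4 | 0.24 | 71%, 81% | 42%, 54% | 48-62% |

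Taking the two methods together, the ranges at 0.05/8 are about 4-7%, 12-18% and 42-62%.

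**After adjustment.** With a rank-based partial Spearman correlation, adjusting for age alone or for age and head size, the simulated rate returned to 4-6% for one test and about 0.3-0.8% at 0.05/8 in every setting.

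**Head size.** This matters only if head size also relates to the outcome. In simulations at n = 126, volume correlated 0.5 with age and 0.5 with head size, and the outcome correlated 0.3 with age. Raising the head size-outcome correlation from 0 to 0.1 moved the false-positive rate from 38% to 59% for one test, and from 13% to 28% at 0.05/8. At 0, head size adds no bias.

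**The case against.** The strongest reply is that the two sections need not describe the same relation. Section 2.8.3 fixes baseline volume. Section 2.8.4 fixes no time point and is about how the intervention works. MRI, microbiota and TMAO are each measured twice, and the primary outcome is a change, so correlating changes is a natural reading. On that reading stable head size and sex largely cancel, and age matters only if it predicts both changes. This stands: the problem belongs to level-on-level correlations. It does not dispose of the point, because 2.8.4 does not say that changes are used and the secondary outcomes are not defined as changes.

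A reader might infer that age and head size are bound to produce significant brain correlations here. The article does not support that. It gives no confounder strengths, the calculated rate runs from nominal upward with what is assumed, and head size has no effect unless it is also related to the outcome. Uncorrected rates should not be taken as what the plan would report either, because 2.8.4 applies Bonferroni. With more tests the rates fall further: at 24 tests (three variables by eight outcomes, an assumption) the approximation gives 2-3%, 6-9% and 29-40% for the three pairs, against 0.05/24 = 0.2% nominal.

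Two further replies are that the analysis is labelled preliminary and that an article may leave detail to an analysis plan. The first limits the seriousness. The second carries less weight, because the article spells out adjustment for gray matter volume twice and then names an unadjusted method for it.

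**Conclusion.** The point holds in limited form. As written, 2.8.4 uses an unadjusted correlation for gray matter volume although 2.8.3 adjusts that variable for four covariates, and Bonferroni does not correct for a common cause. If levels are correlated, the false-positive rate per test at 0.05/8 is above the nominal 0.6% in each of the three age-related scenarios: roughly 7 to 12 times with the weakest inputs (4-7%) and far more with the strongest (42-62%). These sizes rest wholly on assumed age correlations, on eight tests and on 126 to 158 participants. If the outcome, or its change, is unrelated to age, age causes no inflation.

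The randomised comparison of LDL-C is untouched. The consequence is confined to the exploratory mechanistic findings, which makes this a worthwhile correction rather than a threat to the trial's main conclusion. The argument does not extend to pairs of TMAO or microbiota with the outcomes: 2.8.3 sets no covariates for them and the calculations did not cover them.

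**What to change.** In 2.8.4, for every pair that includes gray matter volume, replace the simple Spearman correlation with a partial Spearman correlation adjusted for the 2.8.3 covariates: age, sex, years of education and total intracranial volume. In the same place, state whether levels (and at which visit) or baseline-to-week-8 changes are correlated.

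The cost is a sentence or two of text and four degrees of freedom per correlation, for example 120 instead of 124 at n = 126. All four covariates are already needed for 2.8.3, so no new data are required.
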